### Power calculation and sample size

#### Trial power calculation and sample size

Three hundred fifty patients per arm are considered to be sufficient to examine the impact of social action services (intervention) on quality of life (primary outcome). Trial power was estimated using a worst case scenario assuming 5 % attrition at primary outcome measure. With 350 or more participants per arm power will exceed .80 to detect difference in change over time corresponding to an effect size of f = .10 (considered a small effect size) between the intervention and wait-list groups. This power model uses alpha = .05, two tailed, and uses a conservative correlation of *r* = .6 for scores lagged 4 weeks, and *r* = .5 for 12 weeks.

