### Participant timeline

#### Patient questionnaires

Baseline data (including socio-demographic data such as age, gender, disease diagnosis, education, marital status, living status, spirituality and ethnicity) will be collected from both patients and carers prior to randomisation. The patients randomised to immediately receive the service will do so (following any service administrative procedures) and continue to receive it for as long as required as assessed by the service providers in conjunction with service recipients. At week 4 all participants (intervention arm and wait-list arm) will complete the outcome measures. At this point, the patients on the wait-list arm will also commence receiving the service. Measures will be repeated at week 8. those on the wait-list arm will complete an additional questionnaire at week 12. Participants who withdraw from the service will not be required to complete questionnaires as this may be due to deterioration in physical condition, and the risk of sending questionnaires inappropriately if the services are unable to provide updates on their health status.

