### Comparison between arms

Data will be analysed on an intention to treat basis. A linear mixed effect model (LME) will be fitted to each outcome variable at 4, 8 and 12 weeks. The random effects are intercept and slope; which posit that each participant has a “personalized” linear response to treatment. The fixed effects include site, treatment group, and time since entry, and time interactions, which measure systematic differences in the rate of change. The assumption of a common initial mean for all participants is justified by the randomization of participants into treatment groups. A major advantage of the LME model is that is does not require a balanced design; in particular, participant effects can be estimated using incomplete data. However, missing-completely-at-random (MCAR) assumption will be tested, and in case that this assumption is not tenable, multiple imputation procedures will be employed.

Analyses will be conducted to evaluate potential variables associated with dropout in wait-list controls, to prevent that this attrition inflates the apparent treatment effect at 4 weeks by comparing the intervention group with only those in the wait-list group with some particular features. If observed, these confounders will be included in the LME model to reduce the bias of differential attrition on the estimated treatment effect.

Statistical significance will be assessed at the 5 % (two-sided) level. All statistical analyses will be conducted using SPSS v.20.

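### The dropout screen that decides which covariates enter the model covers only the wait-list arm, so it cannot correct selective loss confined to the immediate arm

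*Protocol article*

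**What the plan says.** The section Comparison between arms plans an intention-to-treat linear mixed model with fixed effects for site, group, time and time interactions, and a common initial mean across arms. For attrition it adds: "Analyses will be conducted to evaluate potential variables associated with dropout in wait-list controls". The stated purpose is to stop loss among controls from inflating the week-4 effect. It continues: "If observed, these confounders will be included in the LME model to reduce the bias of differential attrition". No matching search in the immediate arm is described.

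The section Patient questionnaires says: "Participants who withdraw from the service will not be required to complete questionnaires". The reason given there is that withdrawal may reflect physical deterioration. The same section has the wait-list arm start the service at week 4.

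Two further steps are not limited to one arm. Comparison between arms plans a test of the missing-completely-at-random (MCAR) assumption, with multiple imputation if it is not tenable. Missing data plans a complete-case analysis with sensitivity analyses.

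**The concern.** Bias from differential attrition comes from a difference between arms in who is retained. A search in one arm sees half of that comparison. The half left out matters here because of the protocol's own questionnaire rule: before week 4 nobody on the wait-list is receiving the service, so loss through withdrawal from the service falls mainly on the immediate arm. If those lost there are deteriorating, the retained immediate-arm patients look better than the arm as a whole, and the week-4 contrast favours the service. A covariate that explains this loss would not reach the model, because it is not looked for where it acts.

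**Working it through.** **1. The plan's own power figure.** Inputs from Trial power calculation and sample size: "Three hundred fifty patients per arm are considered to be sufficient"; "assuming 5 % attrition at primary outcome measure"; "This power model uses alpha = .05, two tailed"; "uses a conservative correlation of *r* = .6 for scores lagged 4 weeks"; and "power will exceed .80 to detect difference in change over time corresponding to an effect size of f = .10".

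- Evaluable per arm: 350 × 0.95 = 332.5.
- Two-group effect: d = 2f = 0.20.
- SD of a change score: √(2(1 − 0.6)) = 0.8944, so the standardised effect is 0.20/0.8944 = 0.2236.
- Non-centrality: 0.2236 × √(332.5/2) = 2.883. Power = Φ(2.883 − 1.960) = 0.822.

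This agrees with the protocol and is not at issue. It supplies the target of 0.20 SD.

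**2. Bias when a factor drives loss in the immediate arm only.** Assumptions, not in the protocol: a binary baseline factor X is present in half of each arm and lowers the week-4 score by b = 0.3 or 0.5 SD; immediate-arm loss is p0 without X and p1 with X; wait-list loss is unrelated to X; the true treatment effect is zero. The share with X among retained immediate-arm patients is q = (1 − p1)/[(1 − p0) + (1 − p1)]. In the wait-list arm it stays 0.5. Without X in the model the bias is b(0.5 − q).

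| Immediate loss p0 / p1 (mean) | q | 0.5 − q | Bias, b = 0.3 | Bias, b = 0.5 |
|---|---|---|---|---|
| 0% / 10% (5%) | 0.90/1.90 = 0.474 | 0.026 | 0.008 | 0.013 |
| 5% / 15% (10%) | 0.85/1.80 = 0.472 | 0.028 | 0.008 | 0.014 |
| 0% / 20% (10%) | 0.80/1.80 = 0.444 | 0.056 | 0.017 | 0.028 |
| 5% / 35% (20%) | 0.65/1.60 = 0.406 | 0.094 | 0.028 | 0.047 |
| 10% / 50% (30%) | 0.50/1.40 = 0.357 | 0.143 | 0.043 | 0.071 |

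**3. What the screen does about it.** Simulation: 3000 null trials per scenario, 350 per arm, week-4 score adjusted for baseline (r = 0.6, a simplification of the mixed model). X is added only if associated with dropout at p < 0.05 in the arm or arms searched. Ranges cover b = 0.3 and 0.5.

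| Loss: immediate; wait-list | X enters (wait-list screen) | Bias left, SD | Type I error | Type I error, both arms screened or X prespecified |
|---|---|---|---|---|
| 0/10%; 5% | about 5% | 0.009–0.011 | 4.7–5.2% | 5.1–5.3% |
| 5/35%; 20% | about 5% | 0.027–0.041 | 6.8–9.1% | 4.8–5.5% |
| 10/50%; 30% | about 5–6% | 0.039–0.068 | 10.0–15.2% | 5.0–5.4% |
| Mirror: 20%; 5/35% | 100% | about 0 | 4.3–5.4% | 4.3–5.4% |
| No selection: 5%; 5% | 4–5% | about 0 | 5.3–5.5% | 5.3–5.5% |

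At 10% loss in the immediate arm, simulation gave bias of 0.010–0.016 SD (5% vs 15%) and 0.017–0.029 SD (0% vs 20%), with type I error of 5.7–7.4%. The simulated biases agree with step 2, multiplied by about 0.95 for chance entry of X, to within 0.004 SD. With the two-arm screen or a prespecified X, bias is about 0 in every scenario of the table.

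Relative to target: 0.027/0.20 = 14% and 0.068/0.20 = 34%. The mirror row shows that the one-sidedness is the defect: the same loss pattern placed in the wait-list arm is found every time and corrected.

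**The case against.** The strongest reply is that the damaging pattern is extreme: a factor must drive loss in one arm and hardly at all in the other. Illness and death, which the design section says to expect, act in both arms, and a variable found among controls enters the model for everyone. This largely stands. With immediate-arm loss of 5% vs 35% by X, a wait-list gradient of 10% vs 30% let the screen find X in over 99% of trials, with bias about 0. With 15% vs 25% it was found in about 65%, and bias fell to 0.009–0.013 SD. Nor does it bite at the protocol's assumed 5% attrition.

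It is also fair that the MCAR test, the imputation and the sensitivity analyses are not restricted by arm and may flag such loss. But an MCAR test does not name the responsible variables, and none of these steps changes the one-arm rule for entering covariates.

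Three stronger readings are tempting and are not supported.

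- A reader might infer that choosing covariates by a dropout screen in itself undermines the 5% level. With no selective loss, X entered by chance in 4–5% of trials and type I error stayed at 5.3–5.5%. That aspect is a matter of prespecification, and the candidate list and threshold may sit in a plan not shown.
- A reader might infer that the immediate arm is shown to be the more likely source of bias. The protocol gives no loss by arm, and wait-list participants may also withdraw at any time. The questionnaire rule makes the route plausible, no more.
- A reader might charge the screen with the whole bias from outcome-related loss. With 10% lost and a gap of 0.5–0.8 SD, 0.10 × 0.5/0.90 = 0.056 and 0.10 × 0.8/0.90 = 0.089 SD. That includes loss no baseline variable predicts, which a two-arm screen would not remove either.

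**Conclusion.** The point holds in a limited form. The covariate step is aimed at one arm, while the bias it is meant to reduce depends on both, and the protocol's own questionnaire rule opens a route to loss on the side not searched. Where a measured baseline factor drives loss in the immediate arm only, the step works at the chance rate.

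Under 20–30% loss and a factor worth 0.3–0.5 SD, about 0.03–0.07 SD of bias towards the service remains, with type I error of 7–15%. At 5–10% loss the bias is usually about 0.01 SD, reaching about 0.03 SD only if loss is strongly concentrated. It vanishes if the factor also clearly drives wait-list loss. The loss rates, the prevalence and effect of the factor and the p < 0.05 entry rule are assumptions. The protocol supplies the sample size, correlation, significance level and target effect. This is worth correcting because the remedy is cheap, not because the primary result is shown to be biased.

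**What to change.** - Examine dropout, and its recorded reasons, in both arms, with arm-by-covariate terms in the dropout model.
- Name a short list of baseline variables in advance and include them in the primary mixed model, and in any imputation model, whatever the screen shows. Age, diagnosis and living status are already collected (Outcome measures). Site is already a fixed effect, and the common initial mean implies that the baseline score is modelled.
- Use the dropout findings for sensitivity analyses, including some for data not missing at random, because covariates remove only the loss they explain.
- Reconcile the rule on questionnaires after withdrawal from the service with the intention-to-treat statement.

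The first three changes need no new data for the covariates. The cost is revised analysis wording, a few extra model terms and a little more analysis work.

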### Missing data

A complete case analysis will be undertaken with a range of approaches for undertaking sensitivity analyses to access the robustness of the findings with respect to missing data.

### Case-study evaluation analyses

Data analyses will follow a framework analysis approach using a matrix approach informed by the final theory of change. Framework analysis facilitates within and cross case pattern matching and has been used in case studies in palliative and end-of-life care [25, 26]. This analysis will be integrated with trial data so that an understanding of the factors affecting impact can be compared with quantitative impact. Cross case pattern matching will follow to identify thematic factors associated with challenges and successes in creating impact. This should provide information on facilitators, challenges, barriers and strategies for overcoming them.

All qualitative analyses will be performed using NVivo software.

## Handling and storage of data and documents

### Access to data

The designated contact person(s) in each study site will have access to clinical information either contained within the service referral or available within the organisation if the potential participant is known to them already. Patient and carer permission will be required for Lancaster University to access patient contact details in order to post subsequent questionnaires to patient and carer participants. Patient identifiable data will be encrypted and securely transferred. To ensure confidentiality, data dispersed to project team members will have any identifying participant information removed.

Study data (baseline, week 4, 8, 12 questionnaires) will be returned by post to Lancaster University for entry onto an SPSS database. Weekly data on volunteer input will be securely transferred electronically to Lancaster University for entry onto SPSS. Data will be cleaned and quality checked independently from the person entering the data. Range checks will be made for expected data values. An error rate will be reported.

### Confidentiality

Questionnaires will be coded with a unique alpha numeric identifier which will be kept separately from participant contact details. No personal identifying information will be included in the questionnaires. Interviews will be recorded only if the patient consents for this to occur. Interviews will be digitally recorded on an encrypted recorder and transferred as soon as possible to a password protected computer.

### Data storage

Data storage and handling will include locked storage, password protection, encryption and anonymisation of original data. All audio − recordings will be labelled only with participants’ alphanumeric codes and stored securely. Direct quotations from respondents will only be used in such a way as to ensure anonymity.

### Data monitoring

Due to the low risk nature of the intervention, the REC determined that a data monitoring committee (DMC) was not required. Regular meetings of protocol authors and funder representatives will occur where any adverse or unintended effects of trial interventions or conduct will be discussed, and stopping decisions made. Site initiation visits will be made by Lancaster University investigators to explain trial conduct, and an interim audit of site trial procedures will be made by the investigators.

## Discussion

### Risks

The main risk identified is that participants entered into the trial who are randomised to the wait-list condition will potentially receive suboptimal support over that waiting time, if the intervention is found to be of benefit. However a number of factors mitigate against this risk:First, there is insufficient current evidence that such services are of benefit. There are no current trials or comparative studies of such social action services which measure outcomes and recent reviews of the literature about volunteering at the end-of-life argue strongly for well conducted robust evaluations of these services.Second, a relatively short wait period has been chosen to minimise any risks should the service prove to be of benefit. In the UK people are used to short waits for services and are unlikely to feel seriously disadvantaged by a short wait.Third, these social action services are not currently available to participants, and they would not be receiving the potential benefit of these services without the funding available to support this trial.

There is a further risk that these services cause burden, distress or harm rather than the intended benefit. This is unlikely to be the case, as other similar services have had reports of satisfaction, and the service provided is not core clinical work or hands on care but additional social support. The qualitative interview data collected from participants should give an indication of experience which can be used to monitor this possibility. Participants will also have written information given to them, and verbally explained, about the complaints and other procedures to follow if they have any concerns or feedback related to either their service provision or the conduct of the research. The research team and service provider sites will work closely together to monitor any issues and act upon them rapidly.

There is also a risk that patient and carer participants may be concerned or distressed by some of the questions asked within the questionnaire toolkit. This risk will be minimised by using existing well validated standardised tools, which have been tested in a number of similar populations, and in different cultures and contexts. The tools have been carefully chosen to be short and easy to complete to minimise participant burden as much as possible.

Finally, the risk that participants will be contacted to complete subsequent questionnaires or to be invited to interview when they may be too unwell through deterioration in their condition, or that carers may be distressed by such information after a participants’ death will be mitigated by a clear protocol between the sites and the University to ensure that this information is securely transferred to avoid such distress.

### Potential benefits

Whilst no direct benefit to participants has been promised, they may enjoy and benefit from the social action intervention. This intervention can continue after the research phase of the service: services have been asked to provide this service as per their assessment of need, the only difference to usual service provision is the wait period for those allocated to the wait-list condition. Indirectly, our experience of conducting research in palliative care has shown that patients and informal carers have been willing to take part in such studies as a method of reciprocity for the care they have received from palliative care practitioners and in the knowledge that their participation will inform the overall understanding of the provision of care and benefit others in the future; this finding is increasingly being supported by a growing literature [27–29]. In addition, experience with this kind of research shows that patients and carers often appreciate the interest shown in their experience and opinions [30].
